### Outcomes

The primary outcomes consist of expression of miR-126 and miR-146a, the gut microbiome status, and serum level of TNF-α. Secondary outcomes will be serum levels of lipid profiles (TG, total cholesterol, HDL-C, and LDL-C), anthropometric data, fasting plasma glucose level, HbA1c, fasting plasma insulin level, insulin sensitivity (quantitative insulin sensitivity check index [QUICKI]), homeostasis model assessment of insulin resistance (HOMA-IR), and homeostasis model assessment of beta cell function (HOMA-B). All these factors will be measured at onset and end of the study.

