### Sample size

The required sample size is calculated based on data from a previous human study, which assessed the effects of probiotic yogurt consumption on inflammatory biomarkers [49] by considering the serum level of TNF-α as the primary variable. A mean difference in serum TNF-α levels of 0.84 pg/mL between the two groups is aimed to be detected for a specified α of 0.05 and a study power of 80%. Based on the proposed formula for parallel clinical trials [50], we reached a sample size of 33 participants in each group. Assuming a possible drop-out rate of 10%, 36 patients will be enrolled in each group. G*Power 3.1 software was used for the sample size calculation.

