### Stool samples and microbiota assessment

Stool samples will be collected in sterile containers and will be stored at 4 °C until transport to the laboratory at onset and end of trial. DNA extraction from stool samples will be performed with the QIAamp DNA stool Mini kit (Qiagen, Hilden, Germany) following the manufacturer’s instructions. Microbial composition will be identified by QPCR and 16s ribosomal RNA (rRNA) sequencing using primers of six groups of bacteria including *Akkermansia*, *Faecalibacterium*, *Prevotella*, *Bifidobacterium*, *Lactobacillus*, and Bacteroidetes-Firmicutes.

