### Statistical analysis

Statistical analyses will be performed with SPSS software V.23.0 (SPSS Inc., Chicago, IL, USA). Normality of distribution of data will be assessed by the one-sample Kolmogorov-Smirnov test. At first, the primary information of the intervention and control groups will be compared. Continuous data will be presented as means ± standard deviation (SD), and categorical data will be expressed as numbers and percentages. The independent samples *t* test and the Mann-Whitney *U* test will be used for analyzing the differences in parametric continuous and asymmetric variables between the two groups, respectively. The paired *t* test will be used to identify the effect of the intervention in each group. General linear models will be applied to analyze the effects of the synbiotic relative to placebo after adjusting the baseline factors and individuals’ characteristics. The intention-to-treat (ITT) method and the per protocol analysis will be applied for data analysis. The former considers all participants in the trial and ignores anything that happens after randomization such as misallocation and non-compliance. The latter is adjusted for actual treatment. The results of the aforementioned analyses will be compared with each other.

*P* values < 0.05 will be considered as statistically significant.

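### Four unranked primary outcomes share one 0.05 threshold while the trial is sized on TNF-α alone, so the stated 5% alpha and 80% power describe only one of the four

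*Protocol article*

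**What the plan says.** Four places in the protocol article bear on this point.

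- Outcomes: "The primary outcomes consist of expression of miR-126 and miR-146a, the gut microbiome status, and serum level of TNF-α". No order is given. The Objectives section names the same set as the main aim.
- Sample size: the calculation was made "by considering the serum level of TNF-α as the primary variable". The target is specific to that outcome: "A mean difference in serum TNF-α levels of 0.84 pg/mL between the two groups is aimed to be detected". Alpha is set at 0.05 and power at 80% for this comparison. The result is stated as "we reached a sample size of 33 participants in each group", raised to 36 for drop-out. No effect size or power is given for the microRNAs or the microbiome.
- Stool samples and microbiota assessment: composition is measured "using primers of six groups of bacteria". No summary measure or lead group is named.
- Statistical analysis: P "values < 0.05 will be considered as statistically significant". No hierarchy, adjustment or rule for combining the primary outcomes is stated.

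**The concern.** The article gives two accounts of what is primary. The Sample size section gives the full alpha and power to one variable. The Outcomes section lists four outcomes of equal rank, and one threshold then serves for all of them. An error rate of 5% for TNF-α is not an error rate of 5% for the primary set, and 80% power for TNF-α says nothing about the other three.

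The practical risk lies in reporting. With several unranked primary outcomes and a single cut-off, nothing in the article prevents a P value below 0.05 for one microRNA, or for one microbiome measure, from being presented as a positive primary result while the only powered outcome shows no difference. The Discussion section expects the results to serve as clinical evidence of effectiveness, so it matters which result carries that weight.

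**Working it through.** **Inputs from the article.** Four named primary outcomes (Outcomes); six bacterial groups (Stool samples and microbiota assessment); threshold 0.05 (Statistical analysis); TNF-α difference 0.84 pg/mL, alpha 0.05, power 80%, 33 per group before and 36 after 10% drop-out (Sample size).

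**Assumptions.** Two-sided testing, because the sidedness is not stated. The TNF-α standard deviation is not printed and has to be back-solved.

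**Step 1: the plan's own sample size.** Normal approximation: n per group = 2(1.960 + 0.842)² / d².
- With n = 33, d = √(2 × 2.802² / 33) = 0.690, which implies an SD of 0.84 / 0.690 = 1.22 pg/mL.
- The t-test solution gives d = 0.700 and an SD of 1.20 pg/mL.
- Without a printed SD, 33 can be neither confirmed nor refuted.
- For drop-out, 33 / 0.90 = 36.7, which rounds up to 37 against the stated 36. The difference of one patient is immaterial here.

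**Step 2: error rate for the four named outcomes, no true effect on any.**
- Independent tests: 1 − 0.95^4 = 0.185.
- Bound under any dependence: 4 × 0.05 = 0.20.
- Simulated two-sided z tests with equal correlation 0.3 / 0.5 / 0.8: about 17% / 16% / 11%.

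**Step 3: conditional case, microbiome tested as six separate groups.** The count becomes 1 TNF-α + 2 microRNAs + 6 groups = 9.
- Independent tests: 1 − 0.95^9 = 0.370.
- Bound under any dependence: 9 × 0.05 = 0.45.
- Equal correlation 0.3 / 0.5 / 0.8: about 33% / 27% / 17%.

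Steps 2 and 3 do not depend on the missing SD.

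**Step 4: what splitting alpha would cost.** Power ≈ Φ(d√(n/2) − z(1 − α/2)), with d√(n/2) = 0.690 × √16.5 = 2.80.

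| Tests | Alpha per test | z | Power, normal | Power, t test | Completers per group for 80% |
|---|---|---|---|---|---|
| 1 | 0.05 | 1.96 | 80% | 80% | 33 |
| 4 | 0.0125 | 2.50 | Φ(0.30) = 62% | 61% | about 47–48 |
| 9 | 0.0056 | 2.77 | Φ(0.03) = 51% | 49% | about 55–56 |

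Only 36 per group are to be enrolled. An equal split of alpha therefore does not fit the planned sample, whereas a single TNF-α primary test does.

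**The case against.** The strongest reply has four parts.

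**The count of nine is an inference.** The stool section describes an assay. Nowhere does the article say that the microbiome outcome consists of six primary tests, and a summary measure may be defined in a document not shown. This stands. The figure that rests on stated text is 18.5%; 37% is conditional. Nor is 37% a ceiling: it is the value for nine independent tests, and the strict bound is 45%. Independence is also doubtful, since the trial's own hypothesis links microbiota change to microRNA expression. Positive correlation lowers the figure.

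**No success rule is stated.** A reader might infer that any one P value below 0.05 makes the trial positive. The article does not say so, nor does it say that all four must succeed. That part of the objection stands too. What remains is that the article does not exclude the any-one reading.

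**Adjustment is often left to an analysis plan.** True, and a missing adjustment procedure would not by itself be a finding in a condensed article. But the article itself fixes four primary outcomes, one sizing variable and one threshold. An analysis plan could add a procedure, yet it would inherit the question of which outcome is primary.

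**The sizing phrase may mean only the variable chosen for the calculation.** That reading is possible. It softens the conflict in wording, but it leaves three primary outcomes with no stated power and the same unranked set at 0.05.

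**Conclusion.** The point holds in a limited form. The article names four unranked primary outcomes, sizes the trial on one, and states one threshold of 0.05 with no hierarchy or adjustment. With no true effects, the chance of at least one false-positive primary result is about 18.5% for four independent tests and at most 20%; moderate to strong positive correlation still leaves it at about 11% to 17%. If the six bacterial groups were tested separately, the figure would be about 37% under independence and at most 45%.

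The documents do not support the stronger readings that nine primary tests are planned, that 37% is a maximum, or that success on any one outcome is the declared criterion. The power figures for a split alpha also assume two-sided testing and a d of about 0.70 back-solved from 33 per group.

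One further source of flexibility was not counted: the Statistical analysis section plans both unadjusted comparisons and adjusted linear models, in both intention-to-treat and per-protocol sets.

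**What to change.** Reconcile the Sample size, Outcomes and Statistical analysis sections as follows.

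- **Primary:** the between-group comparison of 12-week serum TNF-α, as the single primary test at two-sided 0.05. This matches the existing sizing and keeps 33 completers per group.
- **miR-126, miR-146a and the microbiome:** either key secondary outcomes, or primary outcomes tested only after TNF-α succeeds, with Holm adjustment across them. Handle the bacterial groups as one multiplicity-controlled family.
- **Remaining outcomes** (glycaemic, lipid, anthropometric): label as unadjusted and exploratory.

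The trial was registered in March 2019, and recruitment began in September 2019 and is ongoing. The change is therefore more than an edit of wording: make it as a dated amendment with its reason, update the registry entry, and complete both before unblinding.

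The cost is that the microRNA and microbiome outcomes, which carry much of the trial's stated novelty, lose co-equal primary status or become conditional on TNF-α. No extra patients or measurements are needed. Splitting alpha would keep all the outcomes co-equal, but at the planned size TNF-α power would fall to about 61% over four tests or 49% over nine, on the assumptions above.

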### Dietary intake and physical activity assessment

Participants will be requested to complete 3-day food record and physical activity record forms, including one weekend day and two weekdays at the beginning and end of the study (one in the first week and the other one in the last week of the intervention), to ensure lack of change in dietary intake and participants’ physical activity during the survey. Daily nutrient intakes will be analyzed using Nutritionist IV software (First Databank, San Bruno, CA, USA), in which the database was modified for Iranian foods. Physical activity records will be analyzed using metabolic equivalent task-hours (MET-h)/day values for every physical activity [51], regarding the time spent by each individual.

### Anthropometric assessment

Anthropometric indices will be quantified at the onset and end of the intervention. Height will be measured, with the participant at a standing position next to the wall, without shoes, to the nearest 0.1 cm with a stadiometer (Seca, Hamburg, Germany); waist and hip circumferences will be taken with minimal inspiration to the nearest 0.1 cm at the smallest waist circumference area with non-stretching tape. Waist-to-height and waist-to-hip ratios will be calculated via standard equations. Body weight will be measured to the nearest 0.1 kg, with the participant in a fasting state, without shoes, and wearing only light clothing, using a weighing calibrated scale (Seca, Hamburg, Germany). Body mass index will be calculated by dividing the body weight in kilograms by the height in meters squared.

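### As worded, the anthropometry rule sites both the waist and the hip tape at the narrowest waist; applied literally, the waist-to-hip ratio would be about 1.00 and could not show a change

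*Protocol article*

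**What the plan says.** In the protocol article, Anthropometric assessment, the tape rule reads: "waist and hip circumferences will be taken with minimal inspiration to the nearest 0.1 cm at the smallest waist circumference area with non-stretching tape". The sentence has a compound subject (waist and hip) and a single measuring site. The next sentence builds two indices on these readings: "Waist-to-height and waist-to-hip ratios will be calculated via standard equations".

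The same section sets two timepoints: "Anthropometric indices will be quantified at the onset and end of the intervention". The Outcomes section places "anthropometric data" among the secondary outcomes without naming individual indices. The waist-to-hip ratio also appears in the Abbreviations list, with no measuring site. No section gives the hip a site of its own.

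The Trial status section reports that recruitment began in September 2019 and was continuing.

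**The concern.** A girth taken at the narrowest waist is not a hip girth. The rule therefore sits badly with the index derived from it: dividing one waist reading by another carries no information about fat distribution.

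This differs from an article merely leaving out a landmark, which would be unremarkable. Here a site is stated, and as worded it is the wrong one for the hip.

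What is at stake is one derived index within a secondary outcome. If the sentence were followed literally, the between-group comparison of the ratio would be null by construction, and a reader of the results could take that as evidence that the synbiotic does not affect fat distribution.

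**Working it through.** The plan gives no figure to reproduce; the point turns on a measurement definition. The article reports no girths, so every girth and error SD below is an illustrative assumption.

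**1. The literal rule without reading error.** Waist-to-hip ratio = waist / hip. If both tapes go round the narrowest waist, hip = waist = W, so the ratio is W / W = 1.000 at each visit. The change is 1.000 - 1.000 = 0, whatever W does.

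**2. The literal rule with reading error.** This was simulated with 200,000 participants per scenario. True waist was uniform on 80 to 120 cm, each reading had independent error, and readings were rounded to 0.1 cm. The true waist change was set to 0, -2 or -5 cm.

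| Reading-error SD | Mean ratio at onset | SD of ratio at onset | Mean change in ratio | SD of change |
|---|---|---|---|---|
| 0 cm | 1.000 | 0 | 0.000 | 0 |
| 0.5 cm | 1.000 | 0.007 | 0.000 | 0.010 |
| 1.0 cm | 1.000 | 0.014 | 0.000 | 0.020 to 0.021 |

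The mean change is 0.000 in all three waist-change scenarios, so the ratio carries only reading error.

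A hand check agrees. The SD of the ratio is approximately √2 × error SD / waist. At a waist of 100 cm this is 1.414 × 0.5 / 100 = 0.007 and 1.414 × 1.0 / 100 = 0.014. The SD of the difference between two visits is √2 times larger, about 0.010 and 0.020.

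**3. A separate hip site, for contrast.** Assume a waist of 100 cm at onset and a hip of 105 cm that does not change.

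- Onset: 100 / 105 = 0.952.
- After a 2 cm waist loss: 98 / 105 = 0.933, a change of -0.019.
- After a 5 cm waist loss: 95 / 105 = 0.905, a change of -0.048.

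The literal rule would replace both changes with zero.

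**4. What is not touched.** Waist circumference, waist-to-height ratio, weight and body mass index do not use the hip reading. Neither do the primary outcomes or the sample size.

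**The case against.** The strongest reply is that this is a compressed sentence and not a measurement plan that anyone would follow. The site phrase names the waist, so it most naturally belongs to the waist reading, with the hip caught in the same clause. The section treats waist and hip as two circumferences and derives a ratio between them, which makes sense only if they differ. This reply largely stands: a drafting slip is the likeliest explanation, and the simulation shows what same-site readings would produce, not that staff take them.

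It does not remove the need for a correction. On either reading, the sentence as printed gives the hip a site that cannot be right.

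A reader might infer two stronger points, and the article supports neither. The first is that the trial's waist-to-hip ratio is already invalid; nothing in the article shows how hips are actually measured. The second is that staff will pick their own hip levels and so add noise between visits. The article does not say how many people take the measurements or what working instructions they have, and a detailed measuring procedure may well sit in the full protocol, which is not shown. No size should be put on such an error.

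It is also fair to say that the endpoint is peripheral. The Outcomes section does not name the ratio, and the Objectives section lists no anthropometry among its secondary aims.

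**Conclusion.** The point holds as a wording error with a conditional consequence. As printed, the section assigns the waist site to both girths. If that is applied literally, the waist-to-hip ratio is about 1.00 for every participant at both visits and cannot show a change. The condition matters, because the sentence is probably a slip.

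The reach is small: hip circumference and the waist-to-hip ratio only, within the secondary anthropometric data. That a ratio of same-site readings is uninformative does not depend on the assumed girths. The contrasts of -0.019 and -0.048 do depend on them and serve only to show the scale of what would be missed. This is a minor correction, worth making because it is nearly free.

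**What to change.** In Anthropometric assessment, split the sentence. Restrict the stated site to the waist, give the hip its own site (the widest level over the buttocks), and state that the same sites are used at onset and end.

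Because recruitment was under way, confirm how hips were measured in participants already enrolled. If they were taken at a proper hip level, only the text needs correcting. Do not report the ratio for any participant whose hip was taken at the waist; waist circumference and waist-to-height ratio remain usable for them.

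Such a participant should not simply be switched to the correct site at the end visit. With the girths assumed above and no bodily change, the ratio would go from 100 / 100 = 1.000 to 100 / 105 = 0.952, an artificial change of -0.048.

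The cost is one sentence, a short reminder to measuring staff and a check of the measurements already taken. No visit, equipment or sample size changes.

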### Blood sampling, biochemical assessment

After 12 h of fasting, a 10-mL venous blood sample will be collected from each participant at baseline and end of trial. A 5-mL blood sample will be collected in test tubes containing clot activator and centrifuged at room temperature, at 3000 rpm for 10 min (Eppendorf AG, Hamburg, Germany) for serum isolation. Serum samples will be stored at − 70 °C. The remainder of the blood sample will be collected in two tubes containing ethylenediaminetetraacetic acid (EDTA) for separate RNA extraction and HbA1c measurement. Biochemical analyses will include serum lipid profiles (TC, HDL-C, LDL-C, TG) and fasting blood glucose using the enzymatic colorimetric method by commercial kits (Pars Azmoon, Tehran, Iran). HbA1c will be measured by high-pressure liquid chromatography (Pars Azmoon, Tehran, Iran). Serum insulin and TNF-α will be assessed using an enzyme-linked immunosorbent assay (ELISA) kit. HOMA-B, QUICKI, and HOMA-IR will be calculated [52]. To keep patient confidentiality, all laboratory information will be saved using an ID number.

### Molecular measurements

MicroRNAs (miR-126 and miR-146a) will be extracted directly from whole blood using Bio Basic purification kit protocol (Bio Basic, Markham, ON, Canada). After normalization, miRNAs will be reverse transcribed to complementary DNA (cDNA) with a Bon-Mir First Strand cDNA Synthesis Kit (Bonyakhteh, Tehran, Iran) according to the manufacturer’s instructions. MiRNA gene expression will be investigated with the real-time polymerase chain reaction (PCR) method, using a Rotor Gene 6000 machine (Corbett, Concorde, NSW, Australia) with a BONmiR quantitative PCR (QPCR) Kit (Bonyakhteh, Tehran, Iran). The relative amount of miRNAs (fold change) will be calculated according to the method 2^–ΔΔCt^ (Livak) [53].

### Stool samples and microbiota assessment

Stool samples will be collected in sterile containers and will be stored at 4 °C until transport to the laboratory at onset and end of trial. DNA extraction from stool samples will be performed with the QIAamp DNA stool Mini kit (Qiagen, Hilden, Germany) following the manufacturer’s instructions. Microbial composition will be identified by QPCR and 16s ribosomal RNA (rRNA) sequencing using primers of six groups of bacteria including *Akkermansia*, *Faecalibacterium*, *Prevotella*, *Bifidobacterium*, *Lactobacillus*, and Bacteroidetes-Firmicutes.

### Statistical analysis

Statistical analyses will be performed with SPSS software V.23.0 (SPSS Inc., Chicago, IL, USA). Normality of distribution of data will be assessed by the one-sample Kolmogorov-Smirnov test. At first, the primary information of the intervention and control groups will be compared. Continuous data will be presented as means ± standard deviation (SD), and categorical data will be expressed as numbers and percentages. The independent samples *t* test and the Mann-Whitney *U* test will be used for analyzing the differences in parametric continuous and asymmetric variables between the two groups, respectively. The paired *t* test will be used to identify the effect of the intervention in each group. General linear models will be applied to analyze the effects of the synbiotic relative to placebo after adjusting the baseline factors and individuals’ characteristics. The intention-to-treat (ITT) method and the per protocol analysis will be applied for data analysis. The former considers all participants in the trial and ignores anything that happens after randomization such as misallocation and non-compliance. The latter is adjusted for actual treatment. The results of the aforementioned analyses will be compared with each other.

*P* values < 0.05 will be considered as statistically significant.

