### Intervention

The intervention group will take two capsules of synbiotic per day (one capsule after lunch and one after dinner), and the control group will take two capsules of placebo (containing 500 mg lactose, magnesium stearate, and talc) per day at the same times for 12 weeks. The synbiotic and placebo capsules look and smell identical and will only be differentiated by a label “A” or “B” on the box. The boxes will be labeled by a third party who is not involved directly in this study. Each synbiotic capsule (Familact, produced by Zisttakhmir Company, Tehran, Iran) contains 500-mg levels (109 colony-forming units [CFUs]) of seven beneficial bacteria (*Lactobacillus casei* 3 × 10^8^ CFU/g, *Lactobacillus acidophilus* 2 × 10^8^ CFU/g, *Lactobacillus bulgaricus* 2 × 10^9^ CFU/g, *Lactobacillus rhamnosus* 3 × 10^8^ CFU/g, *Bifidobacterium breve* 2 × 10^8^ CFU/g, *Bifidobacterium longum* 1 × 10^9^ CFU/g, and *Streptococcus thermophilus* 3 × 10^8^ CFU/g), along with a prebiotic fructooligosaccharide (contributing to the growth and activity of probiotics) and other components (lactose, magnesium acetate, talc). Each box contains 30 capsules. Participants will be given six boxes for the entire 3-month intervention (two boxes at the beginning of each month). Moreover, patients will continue to take diabetic medication during the study. The Diabetes Clinic Center in Yazd and Shahid Sadoughi University of Medical Sciences will be responsible to follow up any reports from participants for any potential relevant issues and adverse events. Any possible adverse events will be reported to the medical ethics committee throughout the study. Participants will be informed at the beginning of the study via the consent form that they have the right to withdraw from the study at any time for any reason or even for no reason.

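### The within-arm paired t test is given the job of identifying the intervention effect, but it measures change from baseline; effect conclusions should rest on the between-arm model that is already planned

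*Protocol article*

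**What the plan says.** The Statistical analysis section of the protocol article describes three kinds of comparison in consecutive sentences.

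- Between arms, unadjusted: the independent-samples t test or the Mann-Whitney U "test will be used for analyzing the differences in parametric continuous and asymmetric variables between the two groups, respectively".
- Within each arm: the paired t "test will be used to identify the effect of the intervention in each group".
- Between arms, adjusted: "General linear models will be applied to analyze the effects of the synbiotic relative to placebo after adjusting the baseline factors and individuals’ characteristics".

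A single threshold covers all of them: P "values < 0.05 will be considered as statistically significant". No sentence says which comparison settles whether the synbiotic works.

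The Sample size section is built on a contrast between arms: "A mean difference in serum TNF-α levels of 0.84 pg/mL between the two groups is aimed to be detected". The Intervention section adds that "patients will continue to take diabetic medication during the study".

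**The concern.** A paired test in one arm asks whether the mean moved between baseline and week 12. It has no comparator, so it cannot separate the synbiotic from anything else that moves the outcome over those weeks. The stated purpose fails most plainly in the placebo arm, which receives no synbiotic and so has no such effect to identify.

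A shared change is plausible in this population. Under Inclusion criteria, patients were diagnosed within the previous six months and are on diabetes medication, which they continue. Entry also requires an HbA1c between 6.5% and 8.5%, so glycaemic measures may regress towards the mean.

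What is at stake is the reading of a disagreement. If the synbiotic arm moves significantly and the adjusted between-arm difference does not reach significance, the wording lets the first result be called an effect. The opening recurs across endpoints: the Outcomes section names two microRNAs, microbiome status and TNF-α as primary, and the stool analysis covers six bacterial groups.

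**Working it through.** **The plan's own figure.** The Sample size section gives a difference of 0.84 pg/mL "for a specified α of 0.05 and a study power of 80"%, and "we reached a sample size of 33 participants in each group". The SD is not stated, so the figure cannot be strictly reproduced, only solved for the SD it implies. With a two-sided test,

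n per arm = 2 × (1.96 + 0.84)² × SD² / 0.84².

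An SD of 1.0 gives 23, 1.2 gives 33 and 1.5 gives 51. So 33 per arm fits an SD of about 1.2 pg/mL in a two-group comparison. The trial is therefore sized for the contrast between arms, not for change within an arm.

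**Inputs for the error rates.** From the protocol article: 33 per arm (Sample size) and a 0.05 threshold (Statistical analysis). Assumed: two-sided tests, normal change scores, equal SD of change in both arms, and a true mean change that is the same in both arms, so that there is no synbiotic effect. The shared change is expressed in SDs of change. The documents do not give it, so a range is shown.

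**Formulas.** Let p be the probability that one arm's paired test shows significant improvement. The paired statistic has 32 degrees of freedom, critical value 2.04, and non-centrality (shared change) × √33. At 0.35 SD this is 0.35 × 5.745 = 2.01, almost at the critical value, so p is close to one half.

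The arms are independent, so P(synbiotic improves significantly, placebo not significant) = p(1 − p) once the chance of significance in the wrong direction is negligible. This has its maximum at p = 0.5, where it is 0.25. With no shared change that chance is not negligible, and the value is 0.025 × 0.95 = 0.024.

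**Results.** Simulation of 100,000 trials per setting, 33 per arm, no synbiotic effect:

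| Shared change (SD) | Synbiotic arm improves significantly | Synbiotic improves significantly, placebo not significant | Exactly one arm significant, either direction | Between-arm t test, two-sided |
|---|---|---|---|---|
| 0 | 2.5% | 2.4% | 9.6% | 5.0% |
| 0.2 | 19.8% | 15.9% | 31.8% | 4.9% |
| 0.35 | 49.6% | 25.1% | 50.0% | 5.0% |
| 0.5 | 79.4% | 16.4% | 32.7% | 4.9% |
| 0.8 | 99.4% | 0.6% | 1.2% | 5.1% |

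Check of the third column against the formula: at 0.2 SD, 0.198 × 0.802 = 0.159; at 0.5 SD, 0.794 × 0.206 = 0.164.

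With 36 per arm the picture is the same: the third column again peaks at 25.1% and the fourth at 50.2%. About half of the between-arm rate, 2.5%, favours the synbiotic. The between-arm column is an unadjusted t test on change scores; the adjusted model was not simulated.

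**The case against.** The strongest defence is that the right analysis is already in the plan. The sentences on either side of the paired test describe between-arm comparisons, one of them explicitly synbiotic relative to placebo with baseline adjustment. The sample size targets a between-arm difference, and the secondary objectives compare changes between the groups. Because the paired test is applied in both arms, it can be read as an ordinary account of pre-post change, loosely worded. Nowhere does the article say that benefit will be concluded from paired tests, or from significance in one arm and not the other. This stands: a reader might infer that the plan discards the randomisation, and the text does not support that.

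A reader might also infer that up to half of null trials would yield a false claim of benefit. That is not supported either. The only quantity with a maximum near 50% is exactly one arm being significant, which includes trials where only placebo changes. The synbiotic-only pattern peaks at about 25% and is 2.4% with no shared change. The synbiotic arm read alone is not capped at half.

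The mechanism also needs limits. The HbA1c window selects on a secondary outcome, so regression to the mean from it bears mainly on glycaemic measures. For TNF-α, the microRNAs and the microbiome, a time trend or medication effect is possible, but the documents give neither its size nor its direction.

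What the defence does not remove is the sentence itself. It assigns the paired test a purpose it cannot serve. That is a misstatement in the text, not a detail left to a fuller plan.

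**Conclusion.** The point holds as a mis-assigned purpose for one planned test. The paired t test describes change over time and cannot identify the effect of the synbiotic. The harm is conditional: it arises only if conclusions are drawn from the within-arm results, which the text permits but does not prescribe.

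In that event the size depends on an assumed shared change. Over 0 to 0.8 SD with no synbiotic effect, the synbiotic arm alone would show significant improvement in about 2.5% to 99% of trials. The synbiotic-only pattern would appear in 0.6% to 25%, highest near 0.35 SD. The between-arm test keeps its 5% whatever the shared change. The randomisation, the sample size and the planned between-arm analyses are not called into question by this point.

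**What to change.** Three changes to the Statistical analysis section:

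1. Remove the statement that the paired t test identifies the intervention effect.
2. Report the mean change within each arm with a confidence interval, labelled as description only.
3. State that every conclusion about effect rests on the baseline-adjusted between-arm difference from the general linear model.

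The cost is wording. No new data, patients or analyses are needed, because the between-arm model is already planned. The article reports recruitment as ongoing and blinding as held until data analysis, so the clarification can be recorded before anyone sees results by arm.
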